### Sample size calculation

2.9

This study is a RCT. The test group was administered QZYLP Granules, while the control group was placed on a placebo. The primary outcome measure was the postoperative DFS of patients. The study was designed as a superiority trial with a 1:1 ratio between the test and control groups. According to the literature, the mDFS for patients with lymph node-positive esophageal squamous carcinoma after surgery with adjuvant therapy is 19.3 months (19). Assuming that the DFS of the test group was 12 months longer than that of the control group, with α=0.05 and 1-β=0.80, the expected time to enroll all participants was 24 months, and the total duration of the clinical trial was expected to be 36 months, with a consistent enrollment rate of the study participants. Using PASS 11 software, it was calculated that 140 cases were needed in each of the test and control groups. Considering a 10% dropout rate, 155 participants were enrolled in the test and control groups, resulting in a final number of 310 participants. The following formula was used (20). Here δ=π_1_-π_2_.

$$n={\left(\frac{u_{\alpha }+u_{\beta }}{\delta }\right)}^{2}[\pi_{1}(1-\pi_{1})+\pi_{2}(1-\pi_{2})]$$

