**Methods:**

This study is a multicenter, randomized, double-blind, placebo-controlled clinical trial. It seeks to enroll 310 patients from 10 hospitals who have completed adjuvant therapy following R0 surgery for esophageal squamous cell carcinoma without recurrent metastasis. Using a center-randomized design, participants will be assigned to the control group (n=155, receiving placebo treatment) or experimental group (n=155, receiving QZYLP granules treatment). Treatment will last for 6 months, with follow-up every 3 months after the final treatment or endpoint event, continuing for up to 3 years postoperatively. The primary outcome measured is DFS at 1 year postoperatively. Secondary outcomes included indicators related to prognosis, fat distribution, peripheral blood inflammation, tumor markers, and quality of life scales.

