### Drop out criteria

2.5

Patients who are unable to adhere to the treatment owing to unforeseen events during the study.Participants who voluntarily request to withdraw from the study.Participants with poor adherence to the study protocol as determined by the investigator.Pregnancy, death, or loss of contact with the participant.

Following termination of treatment or withdrawal from the study, they entered a follow-up period. They received periodic follow-ups (every 3 months, with telephone follow-up accepted) to assess survival status, extending for at least 3 years post-operation.

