#### Secondary outcomes

2.11.2

(1) Prognosis-related indicators:

DFS: Time from randomization to tumor progression or death (from any cause).Overall survival (OS): Time from randomization to death (from any cause).Cumulative annual recurrence and metastasis rate for 1–3 years: Proportion of patients experiencing recurrence and metastasis from the day of surgery to 1, 2, and 3 years.Cumulative annual survival rate for 1–3 years: Proportion of patients surviving from the day of surgery to 1, 2, and 3 years.

(2) Indexes associated with fat distribution:

Total, Visceral, and Subcutaneous Fat Areas: These measure fat areas on cross-sectional images obtained through plain CT scanning.Visceral Adiposity Index: A new assessment of visceral fat based on waist circumference (WC), body mass index (BMI), triglyceride (TG), high-density lipoprotein (HDL), and visceral adiposity index (VAI). Male VAI = during [WC/(39.68 + 1.88 × BMI)] × (TG/1.03) × (1.31/HDL). Female VAI = during [WC/(36.58 + 1.89 × BMI)] × (TG/0.81) × (1.52/HDL).

(3) Tumor markers: squamous cell carcinoma antigen (SCC), carcinoembryonic antigen (CEA), carbohydrate antigen 19-9 CA199), and cytokeratin-19-fragment (CYFR21-1).(4) Peripheral blood inflammatory index: lymphocyte-to-monocyte ratio (LMR); lymphocyte-to-neutrophil ratio (LNR).(5) Prognostic nutritional index: Serum albumin level (g/L) + 5 × total number of peripheral blood lymphocytes (×10^9/L).(6) Symptoms and quality of life evaluation:

Quality of life of the patient: This score was assessed using the Quality of Life Questionnaire Esophageal-Specific Module 18(QLQ-QES18). Each of the 18 questions is scored from 1 to 4, with a total score ranging from 18 to 72. A higher score indicates poorer quality of life.Evaluation of the symptoms of the patients: This score was measured using the M. D. Anderson Symptom Traditional Chinese Medicine (MDASI-TCM). Each of the 26 questions was rated on a scale from 0 to 10, resulting in a total score ranging from 0 to 260. A higher score indicated more severe symptoms.

(7) Medication compliance: The number of cases and percentages were calculated for <80, 80–120, and >120% compliance.(8) Percentage of Participants with Adverse Events: Percentage of participants experiencing adverse events in different study arms.

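### The 36-month total duration in the sample size section contradicts follow-up to 3 years after surgery and the 2- and 3-year secondary rates, which are also defined as crude proportions

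*Protocol article*

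**What the plan says.** Section 2.9 (Sample size calculation) gives the timeline behind the sample size: "the expected time to enroll all participants was 24 months", "the total duration of the clinical trial was expected to be 36 months", "with a consistent enrollment rate of the study participants".

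Follow-up is described differently elsewhere. The Abstract has it "continuing for up to 3 years postoperatively", and section 2.10 (Interventions) likewise sets 3 years after surgery as an upper limit. Section 2.1 (Study design) states follow-up to 3 years after surgery without qualification. Section 2.5 (Drop out criteria), for patients who stop treatment or withdraw, has contact "extending for at least 3 years post-operation".

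Section 2.11.2 (Secondary outcomes) defines the cumulative recurrence and metastasis rate as "Proportion of patients experiencing recurrence and metastasis from the day of surgery to 1, 2, and 3 years", and the survival rate in the same form. Section 2.14 (Statistical analysis) names Kaplan-Meier for survival data, and frequencies, percentages and chi-square tests for count data. It does not say which of the two covers these yearly rates.

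**The concern.** With 24 months of enrolment inside a 36-month trial, follow-up after randomisation ranges from 36 months for the first patient to 12 months for the last. Most patients would not have 3 years after surgery, and many would not have 2 years. A reader cannot tell whether month 36 is the cut-off of the DFS analysis or the end of the trial.

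The outcome definition adds to this. A proportion of patients has a clear meaning only when every patient in the denominator has been observed to the time point. With staggered entry and the planned 10% dropout that will not be so, and a patient not yet followed to 3 years would enter a crude proportion as event-free. The 2- and 3-year rates are a large part of the long-term evidence that the Introduction says is lacking, so their timing and estimator should be unambiguous.

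**Working it through.** **Inputs.** From section 2.9: enrolment 24 months, uniform; total 36 months; control median from "the mDFS for patients with lymph node-positive esophageal squamous carcinoma after surgery with adjuvant therapy is 19.3 months"; effect from "Assuming that the DFS of the test group was 12 months longer than that of the control group", so test median 19.3 + 12 = 31.3 months; α = 0.05, power 0.80. Section 2.14 makes tests two-sided. Exponential DFS from randomisation is my assumption. So is the lag L from surgery to randomisation: section 2.3 requires adjuvant therapy to be completed within 6 months of R0 resection but sets no limit on the time of randomisation. I take L = 0, 3 and 6 months, with 7-9 as sensitivity.

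**Reproducing the plan's figure.** Hazards: ln 2/19.3 = 0.0359 and ln 2/31.3 = 0.0221 per month; hazard ratio 19.3/31.3 = 0.617.
- Events (Schoenfeld): 4(1.960 + 0.842)²/(ln 0.617)² = 134.3, so 135.
- Event probability: 1 − [exp(−12λ) − exp(−36λ)]/(24λ) = 0.5645 control, 0.4053 test.
- N = 135/[(0.5645 + 0.4053)/2] = 278.4, or 139.2 per arm, rounded up to 140 as stated.

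With totals of 54 or 60 months the same calculation gives 98.3 or 92.1 per arm, so the 36-month figure matters to the sample size. One caution: the two-proportion formula printed in section 2.9, evaluated at 24 months (DFS 0.422 and 0.588), also gives 139.5. The article states no 24-month proportion, however, and the enrolment and duration inputs that it lists are those of a time-to-event calculation.

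**Follow-up available at month 36.** A patient randomised at month t has 36 − t + L months since surgery. The share reaching 36 months is L/24, and the share reaching 24 months is (12 + L)/24. All patients reach 12 months. The total needed for the last patient to reach 3 years after surgery is 24 + 36 − L.

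| L (months) | Reach 3 years | Reach 2 years | Total needed |
|---|---|---|---|
| 0 | 0% | 50% | 60 months |
| 3 | 12.5% (39 of 310) | 62.5% | 57 months |
| 6 | 25% (77.5 of 310) | 75% | 54 months |

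For L = 7-9 months the 3-year share is 29-37.5%.

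**Size of the error in a crude 3-year proportion.** The clock runs from surgery, so 3 years is 36 − L months after randomisation.
- True: 1 − exp(−λ(36 − L)).
- Observed over all patients at month 36: 1 − {(L/24)exp(−λ(36 − L)) + [exp(−12λ) − exp(−λ(36 − L))]/(24λ)}.

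| L | Control: observed / true / gap | Test: observed / true / gap |
|---|---|---|
| 0 | 56.45% / 72.55% / 16.1 | 40.53% / 54.94% / 14.4 |
| 3 | 56.25% / 69.43% / 13.2 | 40.34% / 51.85% / 11.5 |
| 6 | 55.59% / 65.95% / 10.4 | 39.71% / 48.54% / 8.8 |

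The gap is also the share of patients misclassified. Both arms are understated, so the between-arm difference moves less: at L = 0 from 72.55 − 54.94 = 17.6 points to 56.45 − 40.53 = 15.9, and at L = 6 from 65.95 − 48.54 = 17.4 to 55.59 − 39.71 = 15.9.

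**The case against.** The strongest reply is that 36 months appears only in the sample size section, while every passage describing the conduct of the trial carries follow-up to 3 years after surgery. On that reading 36 months is the horizon of the DFS calculation, loosely called the trial's total duration. This is plausible, and it stands. A reader might infer that the 3-year outcomes cannot be delivered, but the document does not support that: it holds only if follow-up really stops at month 36.

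A reader might also infer that the three quarters or more of patients without 3 years of follow-up would be miscounted. They would not. Patients with an event before the cut-off are counted correctly, and so are those who stay event-free to 3 years. Only patients event-free at the cut-off who would have an event before 3 years are misclassified. Nor is restriction to early enrolees biased by staggered entry, given uniform accrual and no drift over time; it loses precision.

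On the estimator, it is fair to say that section 2.14 names Kaplan-Meier, that this is a condensed article, and that an analysis plan may settle the matter. Nothing states that censored patients will be counted as event-free. What remains is that section 2.11.2 itself words the rates as proportions of patients. The competing-risk point is secondary: with complete follow-up a crude proportion of recurrences already equals the cumulative incidence, so it matters only once censoring has to be handled.

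The difference between up to and at least 3 years is minor, since section 2.5 concerns survival status after stopping treatment or withdrawal.

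**Conclusion.** The concern holds as a contradiction to be reconciled, not as a demonstrated loss of the 3-year data. A 36-month total with 24 months of enrolment is incompatible with 3 years of post-surgery follow-up for all patients, which needs about 54-60 months. It deserves correction because 140 per arm reproduces with the 36-month figure.

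If the trial did stop at month 36, a crude 3-year proportion would understate DFS events by about 9-16 points, or 9-13 for a lag of 3-6 months. This rests on exponential DFS from randomisation at the planned medians, uniform accrual and no dropout. It uses DFS events as a proxy for the recurrence and survival outcomes, for which the article gives no planning rates. The upper limit of 25% with 3 years of follow-up rests on the assumed 6-month maximum lag. The extension of recruitment reported under Trial status would lower these shares further if the total stayed at 36 months.

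The primary 1-year DFS rate is not affected, because even the last patient has 12 months from randomisation and so at least 12 months from surgery.

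**What to change.** 1. In section 2.9, state that 36 months is the analysis horizon of the DFS sample size calculation. State separately that follow-up and the final 2- and 3-year analyses run until the last patient reaches 3 years after surgery, about 54-60 months from first enrolment and longer with the extended recruitment. If the trial really ends at month 36, drop the 3-year rates instead.
2. Use one description of follow-up length in the Abstract and in sections 2.1, 2.5 and 2.10.
3. In section 2.11.2, define the 1-, 2- and 3-year survival rates as Kaplan-Meier estimates, and recurrence/metastasis as cumulative incidence (Aalen-Johansen) with death as a competing event, each with a 95% confidence interval.

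If follow-up to 3 years is already planned, the cost is wording only, and the estimators use data already being collected. The downside is that the stated total duration becomes longer.

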### Study design

2.1

This study is a multicenter, randomized, double-blind, placebo, parallel-controlled clinical trial conducted according to the protocol approved by the Medical Ethics Committee of Guang’anmen Hospital (2022-200-KY-01). It was registered with Clinical Trials (https://clinicaltrials.gov/) under the number NCT05626309. A randomized design is implemented using a centralized randomization system to conceal protocol allocation. The control group receives a placebo, while the experimental group is treated with QZYLP granules. Both groups also undergo conventional symptomatic therapy. Treatment duration spans 6 months, with follow-up continuing for 3 years post-surgery. After completing the final treatment or reaching the endpoint event, all patients entered a post-treatment follow-up period with evaluation every 3 months. The primary endpoint is the 1-year DFS rate after surgery, which is used to measure the proportion of patients who do not experience recurrence, metastasis, or death (from any cause) within 1 year following surgery. **Figure 1** shows the timeline for enrollment, intervention, and evaluation, while **Figure 2** shows the timeline for intervention and follow-up. **Table 1** depicts the study flowchart.

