#### Primary outcome

2.11.1

1-year DFS rate: Refers to the proportion of patients who did not experience recurrence, metastasis, or death (from any cause) within 1 year following surgery. Although OS is the gold standard for evaluating malignant tumor treatment, given the strong correlation between DFS and OS and to control of time costs, the 1-year DFS rate was selected as the primary endpoint to explore long-term efficacy (22).

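### The 80% power at 140 per arm is not shown for the declared primary endpoint: the inputs are those of a time-to-event comparison, and for the 1-year DFS rate they imply about 58% if DFS is exponential

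*Protocol article*

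**What the plan says.** The protocol article declares the primary endpoint in section 2.1: "The primary endpoint is the 1-year DFS rate after surgery, which is used to measure the proportion of patients who do not experience recurrence". Section 2.11.1 repeats it: "the 1-year DFS rate was selected as the primary endpoint to explore long-term efficacy". Both count the year from surgery. DFS as a time-to-event variable is a secondary outcome in 2.11.2, with a different starting point: "DFS: Time from randomization to tumor progression or death (from any cause".

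Section 2.9 (Sample size calculation) words the target differently: "The primary outcome measure was the postoperative DFS of patients". Its control assumption is a median: "the mDFS for patients with lymph node-positive esophageal squamous carcinoma after surgery with adjuvant therapy is 19.3 months". Its effect is a difference in time: "Assuming that the DFS of the test group was 12 months longer than that of the control group". It adds error rates, "with α=0.05 and 1-β=0.80", uniform accrual over 24 months and a total duration of 36 months. It concludes: "Using PASS 11 software, it was calculated that 140 cases were needed in each of the test and control groups". With 10% dropout this becomes 155 per arm, 310 in total. The section then prints a two-proportion formula in π1 and π2 but attaches no values to them. Section 2.14 makes all tests two-sided.

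**The concern.** A proportion at a fixed time is sized from two proportions. Accrual and total duration do not enter that calculation, but they do enter the event count of a log-rank design. The inputs of 2.9 therefore describe one endpoint, while 2.1 and 2.11.1 declare another. The document assumes no 1-year DFS rate in either arm.

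The two endpoints use different amounts of information. The 1-year rate counts only events in the first 12 months, whereas the time-to-event comparison uses events over 12 to 36 months of follow-up. A sample that gives 80% power for the second can fall well short for the first. If it does, a real benefit of the assumed size could easily yield a non-significant primary result, and readers who trusted the 80% would take that as evidence of no effect.

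**Working it through.** **Inputs.** From 2.9: control median 19.3 months, test median 19.3 + 12 = 31.3 months, α = 0.05, power 0.80, 1:1 allocation, uniform accrual over 24 of 36 months. From 2.14: two-sided testing. My assumption, not the protocol's: exponential DFS. The normal quantiles give (1.960 + 0.842)² = 7.849.

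**1. Reproducing 140 as a time-to-event size.**
- Hazard ratio = 19.3/31.3 = 0.617; ln(HR) = −0.4835; squared, 0.2338.
- Events (Schoenfeld) = 4 × 7.849/0.2338 = 134. Freedman's form gives 140.
- Event probabilities with follow-up uniform between 12 and 36 months: 0.564 (control) and 0.405 (test).
- Per arm: 134.3/(0.564 + 0.405) = 138.5 (Schoenfeld), 142.8 (Lachin-Foulkes), 143.9 (Freedman).
- With 140 per arm, expected events are 140 × 0.970 = 136, and log-rank power is 80%.

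The stated 140 is thus reproduced to within 3%.

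**2. The declared endpoint, same medians.**
- 12-month DFS = exp(−ln 2 × 12/median): 65.0% (control), 76.7% (test); difference 0.1168.
- Sum of the two variances: 0.2275 + 0.1789 = 0.4064.
- Printed formula: 7.849 × 0.4064/0.1168² = 234 per arm (237 with pooled variance).
- Power at 140 per arm: Φ(0.1168/√(0.4064/140) − 1.96) = Φ(2.167 − 1.960) = 58%.
- Power at 155 per arm, no losses: Φ(2.280 − 1.960) = 63%.
- Pooled variance gives 57.6% and 61.9%; comparing 12-month Kaplan-Meier estimates on the complementary log-log scale gives 56.8% at 140.
- A one-sided 0.05 test would still need 184 per arm, and would contradict 2.14.

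**3. When the printed formula does give 140.** With 24-month rates (42.2% against 58.8%) it returns 139.5. At 12 months it does not.

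**4. Dependence on the survival shape.** Holding both medians and using a Weibull distribution, with the printed formula and 140 per arm:

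| Weibull shape | 1-year DFS, control / test | Power at 140 per arm |
|---|---|---|
| 0.7 | 60.8% / 70.2% | 38% |
| 1.0 (exponential) | 65.0% / 76.7% | 58% |
| 1.3 | 68.8% / 81.9% | 73% |
| 1.5 | 71.2% / 84.8% | 80% |

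A shape of 1.5 with these medians means a hazard ratio of 0.617^1.5 = 0.484, a much larger effect than the 0.617 that reproduces 140 in step 1.

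**5. Dependence on when the benefit can start.** Under 2.3, patients enter without recurrence, having completed adjuvant therapy within 6 months after resection, while the 1-year clock starts at surgery. If all are disease-free at month 3 and the exponential hazards apply from then, 9 months remain: 72.4% against 81.9%, power 48%. If entry is at month 6: 80.6% against 87.6%, power 36%.

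**The case against.** The strongest objection is that 58% is not a consequence of the protocol alone. Section 2.9 gives medians, not 1-year rates, and no distribution. That stands. A reader might infer that the power is 58%, or that the trial would miss a true benefit about four times in ten. The documents do not support so exact a statement, and a rising hazard with shape near 1.5 would bring the power to 80%. But the protocol states no such shape, and delayed entry pulls the other way.

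A reader might also infer that 140 was certainly a log-rank result. That is not established: the printed formula with 24-month rates gives 139.5, which rounds up to 140. On neither reading does 140 follow for the 1-year rate under exponential DFS.

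Nor does the document clearly carry two rival primary endpoints. The abstract, 2.1 and 2.11.1 all point to DFS at 1 year, and the looser wording in 2.9 may be shorthand. The absence of π1 and π2 would not be a finding by itself in a condensed article.

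What remains is a contradiction in what is printed: a power figure whose stated inputs do not lead to it for the declared endpoint. Section 2.14 does not resolve it, since it lists both chi-square and log-rank tests without tying either to the primary endpoint.

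**Conclusion.** The concern holds in this form: the 80% power claimed in 2.9 is not shown for the 1-year DFS rate. The stated medians, accrual and duration lead to about 138 to 144 per arm for a time-to-event comparison. For the 1-year rate under exponential DFS they lead to about 234 per arm, or about 58% power at 140 and 63% at 155.

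The size of the shortfall depends on the assumptions. It is about 38% to 73% power for Weibull shapes 0.7 to 1.3 with both medians held, and about 48% to 36% if the benefit begins only 3 to 6 months after surgery; the stated level is met only near shape 1.5. The 58% treats the 19.3-month median and the effect as running from surgery, while the 80% for a log-rank test treats them as running from randomisation. The documents do not show which time origin the cited median has.

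It might be inferred that the primary endpoint must be replaced. That does not follow. Correcting the stated power resolves the contradiction; changing the endpoint after recruitment has begun (section 4) is a separate and debatable choice.

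**What to change.** In section 2.9, name the 1-year DFS rate as the endpoint being sized, state the assumed 1-year rates π1 and π2 and how they were obtained, and replace the 80% with the power that 140 and 155 per arm deliver for that endpoint. Under exponential DFS that is about 58% and 63%, to be given with the range over survival shape and entry time. The cost is a text amendment and a less favourable stated power; no extra patients are needed.

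As an option, the sponsor may, before unblinding and by registered amendment, make time-to-event DFS (already defined in 2.11.2) primary, with a log-rank test and a target of about 134 to 140 events. The amendment should say that the 80% power then assumes the 19.3-month median applies from randomisation. The cost is a late change of the declared primary endpoint, which needs a justification independent of the trial's data, and a headline result that is no longer a 1-year percentage.

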### Interventions

2.10

The experimental group was administered QZYLP granules. Patients were administered two small packets in the morning and two small packets in the evening. The medication was dissolved in hot water before administration. Each course of treatment lasted 4 weeks, with six courses in total. The patients will be followed up for up to 3 years after their EC surgery.

The control group was administered a placebo. The placebo was designed to be identical to the experimental drug in terms of the outer packaging, color, shape, and taste. It was prepared from maltodextrin and food coloring. The raw materials of maltodextrin conformed to the relevant provisions of excipients - maltodextrin in the *Chinese Pharmacopoeia 2015 edition, Part Four* (21). The food coloring included caramel coloring, egg yolk coloring, and milk chocolate brown pigment, all of which were edible-grade ingredients. The dosing method was comparable to that of the experimental group.

During the experimental treatment, drugs for managing myelosuppression, nausea and vomiting, diarrhea, abnormal liver and kidney functions, infections, and other symptomatic treatments were allowed concurrently. However, the specific symptoms and the combined use of these drugs were accurately recorded. The following were prohibited: (1) Other antitumor therapies (including chemotherapy, immunotherapy, molecular targeted therapy, and radiotherapy) (2) Chinese herbal decoctions, Chinese herbal injections, and Chinese patent medicine with antitumor effects.

